#### Application of DFC in Wuqinxi Intervention

##### Clinical and neuropsychological data analysis

Statistical analyses will be performed using SPSS version 19.0. Demographic and clinical information of two PD subgroups (wuqinxi group vs. balance group) will be compared across the three timepoints (baseline, 24 weeks, and 12-week follow-up) using two-factor repeated analysis of variance (ANOVA), see Table 1. Pearson’s chi-square test will be used to compare categorical variables (see Table 1). Pearson’s correlation analyses will be applied between temporal properties and cognition (MoCA and cognitive performance in each domain) across two PD subgroups as well as motor severity (UPDRS-III) before the intervention (see Table 2). Then, the same correlation analyses will be used after the intervention and will also be carried out after follow-up (see Table 2). The threshold for statistical significance will be set at *p* < 0.05.

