### Sample Size Calculation and Blinding

Sample size estimation was performed by G^∗^power V3.1 software (Franz Faul, Universitat Kiel, Germany). According to the analysis, at least 44 participants should be recruited (22 participants per group) in order to be able to perform two-factor repeated ANOVA (within-between interaction) with a middle effect size of 0.25 (Cohen, 1988), level of significance of 0.05, and power of 95% (Mayr et al., 2007). Since some participants may need to be dropped from the analysis due to excessive head motion during scanning, 40 participants will be recruited for each PD subgroup and 40 HC will be recruited. According to a similar studies published recently (Fiorenzato et al., 2019; Chen et al., 2021), this sample size should be adequate for replicating the previous effects in Fiorenzato’s study. In order to attract more participants, we will offer generous compensation and long-term health guidance. Every participant will be offered with an individual exercise plan when the whole study was completed. Randomization of PD patients will be done at the website www.random.org. Two researchers will be trained to assess the outcomes, and they will be blinded to group and will not participate in any interventions.

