##### Group differences in dynamic connectivity: temporal and properties and strength

Between-group (wuqinxigroup vs. balance group) differences in dwell time, fractional windows, and number of transitions will be examined using two-factor repeated ANOVA (*p* < 0.05, FDR correction), see Supplementary Table 1. Covariates will include education, levodopa and dopamine agonist equivalent daily doses. Continuously, subject-specific medians corresponding to each group-level state will be estimated and two-factor repeated ANOVA will be used to compare the connectivity strength of each state at each unique regional pairing (*p* < 0.05, FDR correction) between the three timepoints (before intervention, after intervention, and follow-up), see Supplementary Table 1. Finally, two-factor repeated ANOVA will be performed to compare strength abnormalities associated with cognitive deficits by comparing different timepoints of Wuqinxi group and balance group (*p* < 0.05, FDR correction), see Supplementary Table 1.

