## Discussion

To date, little is understood about the neural mechanisms underlying the improvement of cognitive ability in PD patients after mind-body exercise. Previous studies suggested that mind-body exercise can enhance cognitive performance in PD patients (Zhang Y. et al., 2018; Wu et al., 2019; Zhang et al., 2021). Among the various types of mind-body exercises, Wuqinxi has often been recommended as a complement to medicine to treat cognitive impairment (Zhang et al., 2014). Thus, the present study proposes a longitudinal protocol for enhancing cognition in PD patients with Wuqinxi intervention.

Previous studies have shown that dynamic temporal properties can reflect cognitive alterations in PD patients (Kim et al., 2017; Fiorenzato et al., 2019). Two distinct connectivity ‘states’ have been observed in PD patients: one is more frequent and characterized by a predominance of within-network connections, while the other is less frequent and characterized by between-network connections (Fiorenzato et al., 2019). The dwell time and transitions between these two states was significantly correlated with various cognitive domains in PD patients, suggesting that analysis of these states may help to further our understanding of neural mechanisms of cognitive enhancement. DFC provides a method with which to explore the effects of Wuqinxi at the brain network level, complementing the traditional evidence that focuses more on behavioral performance and motor function (Reynolds et al., 2016).

There are a few shortcomings and in this protocol that have to be considered. First, we calculated the simple size following the principles of behavior science (Cohen, 1988), but it may still be small for neuroscience. Second, we cannot exclude that dopaminergic therapy will have some effect on functional connectivity (Berman et al., 2016). Third, the depression/anxiety of patients may will also have effect on functional connectivity (Yan et al., 2020; Wang C. et al., 2021). Further, it is difficult to guarantee that after randomization wuqinxin- and balance-group is strict matched for baseline cognition.

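### The arm comparison treats baseline as an outcome level instead of adjusting for it: a valid test, but less precise than a baseline-adjusted 24-week contrast, and one connectivity-strength sentence is worded as a time effect

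*Protocol article*

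**What the plan says.** All points are in the protocol article.

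- *Application of DFC in Wuqinxi Intervention, Clinical and neuropsychological data analysis*: the two PD subgroups "will be compared across the three timepoints (baseline, 24 weeks, and 12-week follow-up) using two-factor repeated analysis of variance (ANOVA"). No covariate is named here.
- Same part, *Group differences in dynamic connectivity*: dwell time, fractional windows and number of transitions are compared between the arms by two-factor repeated ANOVA. The covariates are education and the dopaminergic dose equivalents. Connectivity strength at each regional pairing is then to be compared "between the three timepoints (before intervention, after intervention, and follow-up"), again by two-factor repeated ANOVA.
- *Sliding Window Approach*: age, gender and education are regressed out of the connectivity matrices.
- *Sample Size Calculation and Blinding*: the calculation is for a "two-factor repeated ANOVA (within-between interaction") with "a middle effect size of 0.25", "level of significance of 0.05, and power of 95"%. It gives "at least 44 participants should be recruited (22 participants per group"), and the plan is that "40 participants will be recruited for each PD subgroup and 40 HC will be recruited".
- *Discussion*: among the shortcomings, "it is difficult to guarantee that after randomization wuqinxin- and balance-group is strict matched for baseline cognition". No remedy in the analysis is attached.

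**The concern.** The trial asks whether 24 weeks of Wuqinxi does more for cognition and dynamic connectivity than 24 weeks of balance training. That is one difference between arms at one visit. The article fixes an omnibus test over three visits instead, with baseline on the outcome side.

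Three consequences follow.

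1. Baseline is measured on every outcome, and its correlation with the later value is used only through differencing, which is less efficient than regression adjustment.
2. Any chance baseline difference, which the authors themselves anticipate, is over-corrected by differencing unless the between-visit correlation is 1.
3. A significant interaction on 2 degrees of freedom does not say whether the arms differ at 24 weeks, at follow-up or both, or which arm did better.

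The connectivity-strength sentence adds a separate risk. Both arms exercise and both are scanned three times, so a change over time shared by the arms is no evidence for Wuqinxi over balance training.

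**Working it through.** **Inputs.** From the article: two arms, three timepoints, f = 0.25, alpha = 0.05, power 95%, 44 in total as the minimum, 40 per PD arm planned (N = 80). Not given and therefore assumed: between-visit correlation ρ (0.5 and 0.7), sphericity, SD = 1 at each visit, compound symmetry, an arm difference d = 0.5 SD at 24 weeks, and a share r of it (none, half or all) kept at follow-up.

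**1. The article's own figure.** For a within-between interaction with k = 2 groups and m visits:

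λ = f²·N·m/(1−ρ), df1 = (k−1)(m−1), df2 = (N−k)(m−1).

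With m = 3, ρ = 0.5, N = 44: λ = 0.0625 × 44 × 3/0.5 = 16.5, df = 2 and 84, power 95.6%. The smallest N (in steps of two) reaching 95% is 44, as stated. With m = 2 at the same ρ it is 54. Since ρ is not stated, this supports a three-level, 2-df test but does not prove it (two levels with ρ = 0.6 would also give 44). The analysis section names the three timepoints outright, so the reading does not depend on the reproduction.

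**2. Power of the planned interaction at N = 80.** The arm differences by visit are (0, d, r·d). With S the sum of squares of these about their mean, λ = (N/4)·S/(1−ρ), df = 2 and 156.

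- r = 0 or 1: S = 0.25 × 2/3 = 0.1667. λ = 20 × 0.1667/0.5 = 6.67 at ρ = 0.5, and 11.11 at ρ = 0.7.
- r = 0.5: S = 0.125. λ = 5.0 and 8.33.

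**3. Power of the baseline-adjusted 24-week contrast.** SE = √[(1−ρ²)·4/N], df = N − 3 = 77.

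- ρ = 0.5: √(0.75 × 0.05) = 0.194; 0.5/0.194 = 2.58.
- ρ = 0.7: √(0.51 × 0.05) = 0.160; 0.5/0.160 = 3.13.

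| ρ | Interaction, r = 0 | r = 0.5 | r = 1 | Baseline-adjusted, 24 weeks |
|---|---|---|---|---|
| 0.5 | 62% | 50% | 62% | 72% |
| 0.7 | 85% | 73% | 85% | 87% |

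**4. Where the loss comes from.** A 1-df test of change from baseline to 24 weeks has 60% power at ρ = 0.5 and 81% at ρ = 0.7. When none or all of the effect is kept at follow-up, the 2-df test is therefore no worse than a change-score test, and the loss comes from not conditioning on baseline. The ratio of the ANCOVA variance to the change-score variance is (1−ρ²)/[2(1−ρ)] = (1+ρ)/2, which is 0.75 at ρ = 0.5 and 0.85 at ρ = 0.7. The 2 degrees of freedom cost power only when the effect partly decays (r = 0.5).

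**5. Sensitivity to imbalance.** Given an observed baseline difference b, change from baseline is off by (1−ρ)·b in size. For b = 0.3 SD this is 0.15 SD at ρ = 0.5 and 0.09 SD at ρ = 0.7. Over repeated randomisations it averages to zero.

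**6. The connectivity-strength sentence.** In the replication part (whole PD versus healthy controls), the parallel sentence ends by naming the two groups. In the intervention part, that place is taken by the three timepoints. Yet the method is still two-factor, the heading speaks of group differences, the paragraph opens with Wuqinxi versus balance, and its last sentence names both arms. The sentence alone states a time effect; its surroundings point to an arm comparison.

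**The case against.** The strongest reply is that repeated-measures ANOVA and baseline-adjusted analysis are both valid for randomised arms, so this is a matter of efficiency. That is correct. A reader might infer that the planned test is biased by baseline imbalance. It is not: the interaction works on differences between visits, so a constant offset cancels, and it is unbiased on average. What stands is the precision loss and the partial sensitivity in step 5.

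A second reply is that the power gap depends on the scenario. This also stands. The gap narrows to 85% against 87% at ρ = 0.7 when none or all of the effect is kept. The scenarios also correspond to f = √(S/12), about 0.10 to 0.12, well below the planning value of 0.25. At f = 0.25, N = 80 and ρ = 0.5 the planned test has 99.9% power. The gain therefore matters for effects smaller than the one planned for. With the same formula, f = 0.25 equals a 24-week difference of 1.06 SD (r = 0 or 1) or 1.22 SD (r = 0.5).

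Two stronger readings should be resisted. One is that the arms are never compared on connectivity strength; step 6 shows that one sentence is ambiguous, no more. The other is that participants who miss a visit are discarded. The article states removal only for head motion. The rest would be inferred from how classical repeated-measures ANOVA usually works, and missing-data rules may stand in a plan not shown.

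Finally, an unseen analysis plan could name the 24-week contrast. But the article does more than stay silent: it positively fixes the model with baseline as an outcome level, and it words the strength contrast.

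**Conclusion.** The point holds as one of efficiency and of naming the contrast. The planned interaction is a legitimate test, but it uses the baseline data less well than adjustment would and does not by itself answer the 24-week question. At 40 per arm, a 0.5 SD difference and compound symmetry, the loss is about 10 to 23 percentage points of power at correlation 0.5 and about 2 to 14 at 0.7, depending on how much of the effect is kept at follow-up. Correlation, effect size and retention are assumptions; the article gives none of them in this form. The connectivity-strength sentence needs correcting because its literal contrast is over time.

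**What to change.** For each continuous outcome, state that the main arm comparison is the Wuqinxi-minus-balance difference at 24 weeks, adjusted for the baseline value of that outcome and reported with its estimate and confidence interval. Make the same difference at the 12-week follow-up secondary. Either of two models serves: ANCOVA at each visit, or a mixed model on the two post-baseline visits with arm, visit, arm-by-visit and the baseline value. Covariates already planned can stay.

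Reword the connectivity-strength sentence so that it names this arm contrast at each regional pairing, and apply the FDR correction to that contrast.

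The cost is wording in the analysis section. No new data are needed, and the software already planned can fit the model. The small downside is that the omnibus 2-df interaction is no longer the main test; it can be kept as a supporting result. If a separate analysis plan already specifies this contrast, the two texts only need to be brought into line.

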## Abstract

**Background:** Parkinson’s disease (PD) is a neurodegenerative movement disease that includes non-motor symptoms such as cognitive impairment. Long-term mind-body exercise has been shown to improve cognitive ability in PD patients, but the methods of assessment and intervention were inconsistent across studies. Wuqinxi is a mind-body exercise that is easy to learn, has few physical and cognitive demands, and is recommended for PD patients. Dynamic functional connectivity (DFC) has been associated with cognitive alterations in PD patients, but no studies have yet explored the effects of Wuqinxi on this association. The current protocol is designed to measure the effects of long-term Wuqinxi intervention on cognition in PD patients, and explore the underlying neural mechanisms through DFC.

**Methods:** A long-term single-blind, randomized trial will be conducted. PD patients and age- and gender-matched HC will be recruited; PD patients will be randomly assigned to either Wuqinxi or balance groups, and HC will all receive health education. The Wuqinxi group will receive a 90-min session of Wuqinxi intervention three times a week for 24 weeks, while the balance group will receive balance exercise instruction on the same schedule. Primary outcomes will include assessment of cognitive domains and dynamic temporal characteristics of functional connectivity. Secondary outcomes will include severity of motor symptoms, mobility, balance, and emotional state. Assessments will be conducted at baseline, at the end of 24 weeks of intervention, and 12 weeks after interventions have ended.

**Discussion:** This study will provide evidence to the effects of Wuqinxi exercise on cognitive improvements in PD patients from the perspective of DFC, and will contribute to the understanding of neural mechanisms underlying cognitive enhancement through Wuqinxi practice.

**Clinical Trial Registration:**www.chictr.org.cn, identifier ChiCTR2000038517.

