##### Clustering analysis

A K-means clustering algorithm will be applied to the windowed functional connectivity matrices to assess the recurring functional connectivity patterns (states), as expressed by the frequency and structure of these states. Then a cluster validity analysis will be performed on the exemplars of all subjects to estimate the optimal number of clusters. We will use a subset of windows (local maxima in functional connectivity variance) as subject exemplars to decrease the redundancy between windows and computational demands. The reproducibility of functional connectivity states will be established using bootstrap resampling and split-half sample methods. The optimal number of clusters will be set to *k* = 2 following previous studies which is determined based on the silhouette criterion of cluster validity index (Rousseeuw, 1987; Fiorenzato et al., 2019).

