#### Replication of the previous effects

##### Clinical and Neuropsychological Data Analysis

Statistical analyses will be performed using SPSS version 19.0. Demographic and clinical information of all PD patients will be compared using two-sample independent *t*-test (see Table 1). Pearson’s chi-square test will be used to compare categorical variables (see Table 1). Pearson’s correlation analyses will be applied between temporal properties and cognition (MoCA and cognitive performance in each domain) in whole PD patients as well as motor severity (UPDRS-III) before the intervention (see Table 2). The threshold for statistical significance will be set at *p* < 0.05.

**TABLE 2 T2:** Correlation between dynamic functional connectivity temporal properties and clinical characteristics (before intervention, after intervention, and follow-up).

		UPDRS-III	MoCA	Cognitive domains				
				I-M	V	L	A	D-M
Dwell time state I	*r*							
	*p*-Value							
Dwell time state II	*r*							
	*p*-Value							
Fractional windows	*r*							
	*p*-Value							
Number of transitions	*r*							
	*p*-Value							

*I-M = immediate memory; V = visuospatial; L = language; A = attention; D-M = delayed memory.*

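### The planned link between DFC and cognition relates same-visit levels only, at an uncorrected 0.05, so it cannot show that change in DFC goes with change in cognition

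*Protocol article*

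**What the plan says.** The Abstract gives two aims: to measure the effect of long-term Wuqinxi on cognition in PD, and to "explore the underlying neural mechanisms through DFC". The Statistical Analysis section pairs a DFC measure with a cognitive score in one kind of analysis only, the Pearson correlation.

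- In the replication part (Clinical and Neuropsychological Data Analysis), the correlations are run at baseline in all PD patients.
- In the intervention part (Clinical and neuropsychological data analysis), "correlation analyses will be applied between temporal properties and cognition (MoCA and cognitive performance in each domain) across two PD subgroups", with UPDRS-III alongside, before the intervention. It continues: "Then, the same correlation analyses will be used after the intervention and will also be carried out after follow-up".
- The only decision rule given is "The threshold for statistical significance will be set at *p* < 0.05". No multiplicity correction is named.
- Table 2 is the shell for these results. Its title begins "Correlation between dynamic functional connectivity temporal properties and clinical characteristics (before intervention, after intervention, and follow-up". It has no split by arm and no change scores.

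The two sections on group differences in dynamic connectivity are different. They name FDR for each DFC comparison, between PD and healthy controls and between the arms over time. For the temporal properties they also list covariates (education and dopaminergic dose). The correlations have neither.

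**The concern.** Three features of the correlations weaken any statement about mechanism.

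First, a correlation at 24 weeks shows that patients with high values on one measure tend to have high values on the other. A stable characteristic shared by the two measures gives that result at every visit, whether or not the intervention moved either of them. The mechanism question is whether patients whose DFC changed also changed in cognition. The design collects the data for that, but no described analysis uses them.

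Second, many correlations are tested at an unadjusted 0.05, in a plan that adjusts its other DFC tests.

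Third, if the arms are pooled after the intervention without adjusting for arm, a difference between arms in both variables produces a correlation even when none exists within either arm.

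At stake is the second aim. Followed as written, the plan would probably produce some nominally significant DFC-cognition correlations, and these could be reported as a mechanism without support for that reading.

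**Working it through.** **1. The plan's own figure.** The correlations have no sample size of their own. The stated minimum of 44 (f = 0.25, alpha 0.05, power 95%) is for the within-between interaction of a repeated ANOVA. With 2 groups, m = 3 visits, and an assumed correlation between visits of 0.5 and sphericity (neither is stated), the noncentrality is f² × N × m / (1 − 0.5) = 0.0625 × 44 × 3 / 0.5 = 16.5 on 2 and 84 degrees of freedom. Power is 0.956, and 44 is the smallest even N that reaches 95%. The figure is reproduced and is not affected by this point. The planned recruitment of 40 per PD arm gives N = 80 for a pooled correlation before exclusions.

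**2. Number of tests.** Table 2 has 4 DFC rows: dwell time in state I, "Dwell time state II", fractional windows and number of transitions. One row for fractional windows is enough because "The optimal number of clusters will be set to *k* = 2", so the two fractions are complementary. It has 7 columns: UPDRS-III, MoCA and five domains ("I-M = immediate memory; V = visuospatial; L = language; A = attention; D-M = delayed memory").

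- Per visit: 4 × 7 = 28. Over three visits: 28 × 3 = 84. The baseline set repeats the replication correlations and is counted once.
- Involving UPDRS-III: 4 × 1 × 3 = 12. Involving cognition: 84 − 12 = 72.
- DFC-cognition tests after baseline: 4 × 6 × 2 = 48.

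**3. Chance findings if no association exists.** Expected false positives are the number of tests × 0.05: 28 × 0.05 = 1.4 per visit, 84 × 0.05 = 4.2 in all, and 48 × 0.05 = 2.4 for the post-baseline cognition tests. These expectations do not depend on independence.

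The chance of at least one per visit does. If the tests were independent it is 1 − 0.95^28 = 0.76. The documents do not give the correlations among measures. Simulation at N = 80, assuming a common correlation within the DFC set and within the clinical set, gives about 0.69 at a correlation of 0.3, 0.59 at 0.5 and 0.40 at 0.7.

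**4. Levels against changes.** As an illustration with assumed inputs, let each measure be 0.6 × a shared stable trait + 0.8 × its own stable trait + independent visit noise with SD 0.6, so that changes in the two measures are unrelated. The expected same-visit correlation is 0.36 / (0.36 + 0.64 + 0.36) = 0.26. In 2,000 simulated trials of 80 patients it averaged 0.26 and was significant in 67%. The change-on-change correlation averaged 0 and was significant in 6%.

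**5. Pooling over arms.** With no correlation within arm, equal arms, and an arm difference of d SD in both variables, the pooled correlation is r = (d²/4) / (1 + d²/4). The chance of significance follows from Fisher's z with standard error 1/√(N − 3).

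| d in both variables | r | Significant, N = 80 |
|---|---|---|
| 0.5 SD | 0.0625/1.0625 = 0.06 | 8% |
| 0.8 SD | 0.16/1.16 = 0.14 | 23% |
| 1.06 SD | 0.281/1.281 = 0.22 | 50% |

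The 1.06 SD is not stated in the document. It is what f = 0.25 implies if the arm difference over the three visits is 0, d, d or 0, d, 0: f² = d²/18, so d = 0.25 × √18 = 1.06. The pattern 0, d, d/2 gives f² = d²/24 and d = 1.22. If exclusions reduce N to 60, the 50% becomes 39%.

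**The case against.** The strongest reply is that the plan does not stake its mechanism aim on these correlations alone. The intervention's effect on dwell time, fractional windows, transitions and connectivity strength is tested by repeated ANOVA with FDR, including a comparison of strength abnormalities tied to cognitive deficits. This stands. A reader might infer that the mechanism as a whole is tested only by uncorrected correlations, and the document does not support that. The ANOVAs as described contain no cognitive change variable, however, so they do not supply the link between DFC and cognition.

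A reader might also take all 84 correlations as tests of mechanism. They are not: the 28 at baseline serve the replication, and 12 of the 84 concern motor severity. The relevant number is 48.

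Pooling is also an interpretation. The replication section says plainly that it uses the whole PD sample, whereas the intervention section refers to the two subgroups, which could mean within each arm. Pooled remains the natural reading because Table 2 has no arm split. If the analysis is within arm, the argument in step 5 falls, but the tests increase to 28 × 2 × 3 = 168 if every visit is split, with 168 × 0.05 = 8.4 expected false positives.

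The arm-induced artefact is appreciable only for large differences in both variables, against an active exercise comparator. At 0.5 SD it is close to the nominal 5%.

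Finally, the aim is exploratory, and an analysis plan not shown may add detail. But this article does fix the method, variables, visits and threshold, so the point concerns a stated method and not missing detail.

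**Conclusion.** The point holds for the link between DFC and cognition. As written, that link is assessed only by same-visit correlations at an uncorrected 0.05. These cannot show that patients whose DFC changed also changed in cognition, and with no true association they yield about 1.4 false positives per visit (2.4 over the 48 post-baseline cognition tests). The 40% to 76% chance of at least one per visit rests on assumed correlations among the measures; the expected counts do not. The pooling artefact is conditional on the arms being pooled and on large effects in both variables, so it is a secondary reason for adjustment.

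A reader might infer that the randomised comparisons are undermined. They are not: the arm-by-time analyses of cognition and of DFC, and the sample size, are untouched. The weakness limits what may be said about mechanism, and it should be corrected before the data are analysed.

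**What to change.** - Add, as the exploratory mechanism analysis, a regression of baseline-to-24-week change in cognition on change in each DFC property, adjusted for arm and for the baseline values of both measures.
- Extend FDR correction to the Table 2 correlations and to this new set, and state which tests form each family.
- Keep the per-visit correlations as descriptive, adjusted for arm after baseline, and say whether the analysis across the two subgroups is pooled or within arm.
- State that an association between the changes is observational even though the arms were randomised.

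The cost is a few more regressions on data already collected, and fewer nominally significant correlations. An arm-by-change term is optional; the trial was not powered for it, so it should be reported as an estimate with its interval.

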#### Primary Outcome Assessment

The Montreal Cognitive Assessment (Nasreddine et al., 2005) will be conducted to assess cognitive impairment and the Repeatable Battery for the Assessment of Neuropsychological Status (Stella et al., 2013) will be used to measure the cognitive domains of immediate memory, visuospatial, language, attention, and delayed memory (see Supplementary Table 1). Dynamic states, dwell times, fractional windows, and number of transitions will be computed to reflect the characteristics of DFC (see Supplementary Table 1).

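### Six unranked cognitive primary outcomes share a plain p < 0.05 while the DFC group comparisons get FDR: the chance of any false cognitive group difference is about 16–27%, or about 8–14% in Wuqinxi's favour

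*Protocol article*

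**What the plan says.** - **Primary outcomes.** The Abstract states: "Primary outcomes will include assessment of cognitive domains and dynamic temporal characteristics of functional connectivity". *Primary Outcome Assessment* lists MoCA and then RBANS, which "will be used to measure the cognitive domains of immediate memory, visuospatial, language, attention, and delayed memory". The same section adds the DFC properties. No outcome is marked as the lead one. The later correlation analyses and Table 2 treat each RBANS domain separately, so the cognitive set has 1 + 5 = 6 members.
- **Cognitive threshold.** Under *Application of DFC in Wuqinxi Intervention*, the subsection *Clinical and neuropsychological data analysis* compares the two PD arms over three timepoints by two-factor repeated ANOVA. It ends: "The threshold for statistical significance will be set at" p < 0.05. It names no correction.
- **DFC threshold.** The next subsection, on group differences in dynamic connectivity, attaches an FDR correction to every DFC group comparison.
- **Sample size.** *Sample Size Calculation and Blinding* says "at least 44 participants should be recruited (22 participants per group") for a "two-factor repeated ANOVA (within-between interaction") "with a middle effect size of 0.25", "level of significance of 0.05, and power of 95" per cent. It then plans: "40 participants will be recruited for each PD subgroup and 40 HC will be recruited".

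**The concern.** The plan recognises multiplicity in the imaging half of its primary set and leaves the cognitive half at a single-test threshold. Six tests at 0.05 do not carry a 5% error rate as a set. With no lead outcome and no rule on how many must be positive, any one of the six could be presented as the cognitive result of the trial. A reader could not tell which test was meant to answer the question. The effect of Wuqinxi on cognition is the trial's main clinical question, so this error rate matters most. The stated 95% power belongs to one test at 0.05 and does not describe a family of six tested at a controlled level.

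**Working it through.** **Inputs from the article:** six cognitive primaries; 0.05 per test; f = 0.25; power 95%; two arms (g = 2), three timepoints (m = 3); minimum N = 44; planned PD recruitment 2 × 40 = 80.

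**Assumptions, not in the article:** within-subject correlation 0.5 and epsilon 1 for power; an equal correlation r between each pair of cognitive outcomes, varied from 0 to 0.8.

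**Step 1. Reproduce the sample size.** For the within-between interaction, λ = f²·N·m/(1 − within-subject correlation), df1 = (g − 1)(m − 1), df2 = (N − g)(m − 1).

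- N = 44: λ = 0.0625 × 44 × 3 / 0.5 = 16.5, df = 2 and 84, power 95.6%.
- N = 42: λ = 15.75, df = 2 and 80, power 94.6%.

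So 44 is the smallest even N that reaches 95%. The stated figure reproduces, as one test at 0.05.

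**Step 2. Error over six tests, all nulls true.**

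- Independent, either direction: 1 − 0.95⁶ = 0.265.
- Independent, Wuqinxi's favour only: 1 − 0.975⁶ = 0.141. A single two-sided test has 0.025.
- Equal correlation r, with c = 1.96: 1 − ∫ φ(x)·[Φ((c − √r·x)/√(1 − r)) − Φ((−c − √r·x)/√(1 − r))]⁶ dx. For the favourable direction alone, drop the second Φ term.

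| r (assumed) | Any false group difference | In Wuqinxi's favour | Any, at 0.05/6 each |
|---|---|---|---|
| 0 | 26.5% | 14.1% | 4.9% |
| 0.3 | 24.1% | 12.2% | 4.6% |
| 0.5 | 20.7% | 10.4% | 4.1% |
| 0.7 | 16.4% | 8.2% | 3.3% |
| 0.8 | 13.9% | 6.9% | 2.8% |

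**Step 3. Check with the planned type of test.** Six 2 × 3 repeated-measures interaction tests were simulated under the global null, 20,000 trials per setting. With 40 per arm, the rate of any false positive was 26.6%, 21.1% and 17.0% at r = 0, 0.5 and 0.7. Counting only false positives whose 24-week change favoured Wuqinxi, it was 14.2%, 10.8% and 9.3%. Results with 22 per arm were close to these. The normal formula is adequate.

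**Step 4. Power at the corrected level.** At f = 0.25 and alpha = 0.05/6 = 0.0083:

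- N = 44 (λ = 16.5): 84.1%.
- N = 80 (λ = 0.0625 × 80 × 3 / 0.5 = 30, df = 2 and 156): 99.2%.

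**The case against.** **The document is condensed and the analysis plan is not shown.** A multiplicity procedure might sit there, and Supplementary Table 1, to which the outcome section refers, is also not shown. This defence is only partial. The article does not stay silent: it fixes a corrected threshold for one part of the primary set and a plain one for the other.

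**The ANOVA sentence names demographic and clinical information, not cognition.** That is so. Cognition comes in through the subsection heading, and MoCA and the domains are named explicitly only in the correlation analyses. But this is the type of test on which the trial was sized. If the sentence excluded cognition, the article would state no between-arm test for its cognitive primaries.

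**The aim is exploratory, and no text says one positive domain is success.** The Introduction does speak of exploring effects. The error rates are therefore conditional on any single positive result being read as an effect, which the article neither states nor rules out.

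**Stronger readings that a reader might infer, and that the article does not support:**

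- *That 16–27% is the chance of falsely concluding that Wuqinxi improves cognition.* The tests are non-directional, and that range includes false results favouring balance training. The favourable share is about half.
- *That the DFC properties should be added to the uncorrected family.* Their group comparisons already carry FDR. The DFC–cognition correlations in Table 2 are under the plain threshold, but they are not between-arm tests and are not counted here.
- *That separate readings at 24 weeks and follow-up inflate the error further.* The plan states one analysis across all three timepoints and no separate group test at each visit.

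**Conclusion.** The point holds in a bounded form. If the plan is followed as written and any one of the six cognitive results may be claimed, the chance of at least one false group difference is about 16–27% against a nominal 5%. In Wuqinxi's favour it is about 8–14% against 2.5%. Either way, the inflation is roughly three- to sixfold. The ranges correspond to assumed between-outcome correlations of 0.7 down to 0. At 0.8 they fall to about 14% and 7%, still well above nominal. The sample size is arithmetically sound for one test, given a within-subject correlation of 0.5 and epsilon 1, neither of which the article states. It does not address six tests.

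**What to change.** In *Clinical and neuropsychological data analysis*, name MoCA and the five RBANS domains as the outcomes of the Wuqinxi versus balance ANOVA. Then do one of two things before outcomes are compared by arm:

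1. Keep all six as primary and apply Holm across the six group-by-time tests, or the FDR already used for DFC. Holm controls the chance of any false positive. FDR controls the expected share of false positives among the claims, which is a weaker guarantee if one domain alone may carry the conclusion.
2. Name one cognitive outcome as the lead primary, tested at 0.05, and adjust the other five.

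Restate power at the corrected level in *Sample Size Calculation and Blinding*, with the within-subject correlation and epsilon given.

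The cost is wording and some power per outcome. At f = 0.25 and the Bonferroni level 0.05/6, power falls from 95.6% to about 84% with 44 patients analysed, and is about 99% with 80, under the assumptions stated above. Holm is never less powerful than Bonferroni. Under option 2 the lead outcome keeps the stated calculation if it is tested by the same three-timepoint interaction. No extra recruitment is needed if most of the planned 80 patients are analysed.
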